### Objectives

#### Principal objective

Assess the effectiveness of the Health Workshops, in terms of HRQOL measured by the SF-36 Questionnaire.

Secondary objectives:

1.) To know the effectiveness of the Health Workshops in relation to:

• Incorporating and maintaining a balanced diet.

• Keeping up a regular physical activity.

• Maintaining risk factors (Blood Pressure, Weight, and Cholesterol) within normal limits.

• Risk reduction cardiovascular disease (CVD)

2.) To make an estimate of the costs of the Health Workshop.

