## Method/Design

Design: Cluster randomized trial, controlled and multicentric, comparing one group of patients that take part in the Health Workshops, with another group of similar characteristics that don't.

Setting: The study will be done in Heath Care Centers of Barcelona City.

Randomization unit: Primary care Teams (PCT)

Study Population: Population around the Centers that participate in the Study and that meet the criteria of inclusion.

Inclusion criteria:

• Persons of both sexes between 18 and 65 who consent to do so.

Exclusion criteria:

• If there is an objection to participating during a period of 12 months.

• If there a language difficulty, unable to understand or express in Spanish or Catalan.

• If there are acute mental problems.

• Other health problems which may be a difficulty in following the workshop, (like terminals, organic pathology...).

Sample size calculation: Accepting an Alfa risk of 0.05 and a Beta risk of 0.2 in a bilateral contrast, 108 individuals per group are needed in order to detect how statistically effective it is in a 20% difference between groups in quality of life with the SF-36 Questionnaire. We have estimated a 10% rate of loss in participation. The ARCOSENO approximation has been used.

Variables in the study: We collect socio-demographic variables from all participants: age, sex, studies, employment or work situation.

Principal Variable: HRQOL measured by means of SF-36 Questionnaire. We have selected the quality of life perceived indicator as the main variable as it is sensible to small changes [19].

Variables related to the intervention:

• Number of sessions the person has attended.

• IPAC Questionnaire for variables related to physical activity (the IPAC questionnaire has been used in research around this area so it allows us to compare the data obtained.)

• The variables related to eating habits will be collected by means of Questionnaire PREDIMED [15], which is validated and used in our area, as so allow us to compare results.

• Blood Pressure, Lipid Profile, Height, Weight, will be gathered from the computerized clinical history.

• To estimate the costs we will add the time spent by professionals directly related with the intervention (telephone calls, meetings with participants, gathering of data, workshops...)

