• Gathering of information: the gathering of data will be done in both groups, (intervention and control groups): before each intervention (Health Workshop), at the end of the intervention and in 6 months and 12 through self administered questionnaires in Teleform^© ^format.

Description of the Study (Figure 1)

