5.	Sleep and rest. Recommendations for a good rest and sleep. Leisure activities. The importance of dedication time to leisure.

6.	Avoid physical and emotional dangers. Self-esteem.

7.	Communication with others and social interaction. Managing one's emotions.

8.	Work and feel useful. The importance of activities that produce a sense of satisfaction.

Each session starts with a breathing exercise that helps participants to center themselves in the group. Next they share the week's experiences and clarify doubts. Followed by the theoretical content about the subject of the session and the practical exercises that to be done during the next week. The session ends with a space to clarify doubts and share reflections that have come up through the exposure of the theoretical concepts.

At the end of each session we hand out texts to be kept in their files and that will form, at the end of the Health Workshop, a MANUAL OF HEALTH CARE AND MAINTENANCE.

We have elaborated specific material, (with slides and points dealt with in the sessions) to ensure the unification of the message given. Also, we have elaborated support and reminder material for each session which gathers all the contents of the sessions. Such material is handed out at the end of each session to be kept in the files provided at the beginning of the Health Workshop, and which will, in the end, form a Manual for Health Self-Care and Maintenance.

The control group will continue to receive normal attention and will have the possibility, if they so desire, of doing the Health Workshops at the end of the Project, (if it has proven effective), once the 12 months are over with the last evaluation.

Phase Closing of the Project

4 Gathering and analyzing the last data and communicating the results.

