### Data analysis

The analysis will be done on an intention to treat basis. Those who have done less than six sessions will be considered withdrawals.

The descriptive analysis will be done in proportion to the quality variables and the average values for the quantities, with the corresponding measures of dispersion.

To observe the effect of the intervention in quality of life related to health, the change of habits and the costs derived from related resources, the T-Tests will be used for paired data and the McNemar Test or equivalents for quantitative or qualitative variables or their non parametric equivalents, if the distribution of the variable does not comply with the criteria of normality (Kolmogorov-Smirnof).

To analyze the factors that have influence over the changes of quality of life related to health (CVRS) and those related with the intervention, models of multiple regressions will be used. In each regression model the dependent variable will be derived from the calculation or the difference between ratings in the beginning of the study and the ratings at the end of the SF-36; the rest of the variables determined in the study will be included as independent variables. As the first step in the analysis of regression the adequate diagnosis will be done to detect extreme values and verify conditions of applicability (homocedastisity, normality and independence of waste). If needed the necessary transformations will be done in the dependent variables for the fulfillment of applicability conditions. The criteria of selection of variables for the estimation of multivariable models will be a Forward-Stepwise with the criteria of input of p < 0.05 and a criteria of output of p > 0.10.

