### Quality control

The proceedings used to guaranty the quality of the information are the following:

• The intervention is done by the persons in the research group who created all the educational material being used in the session, which guarantees a homogenous intervention.

• The gathering of data is done through self-operated questionnaires in Teleform^©^. This automated software that reads scanned questionnaires, performs a validating process of the data with previously established parameters, and once the data is validated these are poured into a specifically created database.

• The introduction of information or data will be performed by a person hired to provide technical assistance for this study.

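### The cost rule counts trial data collection as part of the Health Workshop's cost, and the analysis sends costs to paired tests although no baseline cost is defined

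*Protocol article*

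**What the plan says.** The second of the two numbered secondary objectives reads "To make an estimate of the costs of the Health Workshop". It asks for an estimate and names no comparison, hypothesis or target figure.

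Under Method/Design, in the list of variables related to the intervention, the estimate is formed by adding "time spent by professionals directly related with the intervention (telephone calls, meetings with participants, gathering of data, workshops" and, by an ellipsis, similar activities.

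Two other places show how the article uses the data-gathering phrase. The item on gathering of information in Method/Design says "the gathering of data will be done in both groups, (intervention and control groups", with rounds before the workshop, then "at the end of the intervention and in 6 months and 12 through self administered questionnaires". Quality control says "The gathering of data is done through self-operated questionnaires in Teleform".

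The Data analysis section names the outcomes to be tested as quality of life, "the change of habits and the costs derived from related resources, the T-Tests will be used for paired data", with McNemar or non-parametric equivalents as alternatives.

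**The concern.** Two parts of the cost objective do not fit together.

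- **The cost definition.** Questionnaires filled in for the trial measure the intervention; they do not deliver it. The 6- and 12-month rounds fall after the eight weekly sessions have ended, and controls complete the questionnaires without attending a workshop. A service that wants to know what the workshop would cost in routine use needs a figure without that time.
- **The cost analysis.** A paired before-after test needs two values per unit. Staff time spent on the workshop begins with the workshop, so the variable as defined supplies only one.

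At stake is whether the cost figure can be used by a health service considering adoption. If research time is not separated when it is recorded, it may not be separable afterwards.

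**Working it through.** There is no cost figure in the article to reproduce, so the check is mainly a comparison of its sections.

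1. **What the sum contains.** The Method/Design list gives four kinds of staff time as examples: calls, meetings with participants, data gathering and workshops. Data gathering is therefore counted by name.

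2. **What data gathering means here.** Both other uses of the phrase, in the gathering-of-information item and in Quality control, refer to study questionnaires. The first states that both arms are covered and gives four rounds: before, end of intervention, 6 months and 12 months. Neither describes workshop administration.

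3. **Direction.** If research time is added to delivery time, the stated workshop cost goes up.

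4. **Size.** Let *s* be minutes per session, *g* the group size, *d* the staff minutes per participant per data round, with one professional per session. For an intervention-arm participant:

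   added share = (4 × *d*) ÷ (8 × *s* ÷ *g*)

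   The article gives the 4 rounds, the 8 sessions and *g* = 12 to 15. It does not give *s*, *d* or the number of professionals. Taking *s* = 90 to 120 and *d* = 1 to 30 purely as assumptions:
   - *s* = 120, *g* = 12, *d* = 1: 4 ÷ 80 = 5%
   - *s* = 120, *g* = 12, *d* = 5: 20 ÷ 80 = 25%
   - *s* = 90, *g* = 15, *d* = 30: 120 ÷ 48 = 250%

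   The denominator leaves out calls and meetings, which the rule also counts, so these shares err on the high side. The forms are self-administered and scanned, so *d* could be very small; on the other hand, the study description also has an individual visit for blood pressure and weight, which takes staff time. A range this wide shows only that the article does not determine the size.

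5. **The paired test.** The one cost variable defined is staff time on the intervention, and it has no pre-intervention value. The variables listed in Method/Design include no other resource-use or cost measure. Either the Data analysis section means this variable, and there is nothing to pair, or it means another cost, and that cost is not defined.

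6. **Effect of the test on the total.** None. A summed cost is the same whether or not a test is then attempted on it.

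**The case against.** The strongest reply concerns the qualifier. The rule limits the sum to time directly tied to the intervention, and the item sits beside calls and meetings, so it could mean intake records. The study description mentions application forms with contact details and availability, which routine delivery would also need. This leaves room for doubt about what would actually be counted. It does not settle the matter, because the parenthesis offers data gathering as an example of qualifying time and the article's other uses of the phrase concern trial questionnaires. At best, two people recording time could arrive at different costs.

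It can also be said that the costs named in the Data analysis section carry a different description from the staff time in Method/Design and may be a separate quantity. That is fair. The fault would then be an undefined variable instead of an inapplicable test, and either way the text needs correcting.

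A reader might infer three stronger things that the documents do not support:

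- **The cost will certainly be wrong, by a quarter to more than double.** Any such percentage rests on assumed minutes. Charging control-arm data collection to the workshop would raise it further, but that sits badly with the rule's own qualifier.
- **The paired test distorts the cost figure.** It cannot change a sum.
- **Handouts and files are wrongly left out.** The rule mentions only professional time, although the study description says of the support texts: "Such material is handed out at the end of each session to be kept in the files provided at the beginning of the Health Workshop". Full cost itemisation is, however, detail that a condensed article may leave to the full protocol, so this is not counted as a fault.

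**Conclusion.** The point holds in a limited form. As written, the workshop cost is liable to be overstated by research time. The direction follows if the data-gathering item carries the meaning it has elsewhere in the article; the amount cannot be computed from what the article gives. Separately, costs are assigned to paired tests without any cost variable that has a baseline value. The objective affected is secondary and descriptive. Neither fault touches the SF-36 result or the sample size, but the correction is worth making before time is recorded.

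**What to change.** In Method/Design, define workshop cost as staff time for organising and delivering the workshop. Record trial data-collection time under its own category and exclude it from that cost.

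In Data analysis, take one of two routes: remove costs from the paired tests and report the workshop cost descriptively, which is all the objective asks for; or define a resource-use cost variable with a value at baseline and at follow-up, and say that this is what is tested.

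The first route costs one extra category when staff time is recorded, plus a change of wording, and the stated workshop cost will be lower to the extent that research time would have been counted. It needs no added participants or procedures. The second route would need resource-use data that the article does not now list.

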**Figure 1 F1:**
[figure not shown]
**Algorithm of the study**.

The stages of this study are the following:

Phase Recruitment and selection:

1 The recruitment of the PCT: The project is explained to professionals belonging to the Health Centre. Those interested in participating in the recruiting of patients will sign a commitment of participation in the Project. The participants will be recruited by these professionals and their inclusion will be consecutive. Once the recruitment has ended, the groups will be randomized in the intervention or control group. Persons interested will fill up an application form for the Workshop, which will be available in their Health Care Center (HCC) and where they have to give their name, phone number, and time availability.

The Blood Pressure (BP) and Weight data will be gathered (in those persons who consent), at an individual visit after the informative meeting. They will be asked to have a Lipid Profile (if it is not available in their clinical history in a 3 months period before the workshops begins), and again after 12 months.

Phase The Forming of the Study Groups

2 Based on the persons who have given their consent to participate, an random assignation to one or another group will take place, and the workshops will then start (with groups of 12 to 15 persons in each).

Phase Intervention (only in the group intervened)

3 The group intervention then starts in 8 sessions in which life activities will be approached in a progressive manner. During the sessions, tools will be offered to increase knowledge and develop abilities and motivations that help with life activities and the progressive incorporation of healthy habits. At the end of each session support material will be handed out with the session's contents and indications of activities to practice during the week.

The workshops will be offered at different schedules to facilitate assistance. The contents of the sessions are in Table 1.

**Table 1 T1:** Subject matter of the sessions in the work shop

Session	Content
1	Breathing. Tobacco, learning from experience.

2.	Eating and drinking adequately, a balanced diet.

3.	Elimination. The importance of regular disposal. Guides to avoid constipation. Hygiene. The importance of personal hygiene.

4.	Movement and maintaining adequate positions. Doing physical activity. Wearing adequate clothes.

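### The baseline questionnaires are timed against the start of the workshop, not against allocation, so as written the self-reported SF-36 baseline may be completed after participants know their arm

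*Protocol article*

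**What the plan says.** Method/Design, under the gathering of information, gives one schedule for both groups. The self-completed forms are due "before each intervention (Health Workshop), at the end of the intervention and in 6 months and 12 through self administered questionnaires".

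The description of the study gives the order of events. In the recruitment stage: "Once the recruitment has ended, the groups will be randomized in the intervention or control group". In the stage that forms the study groups, after consent: "an random assignation to one or another group will take place, and the workshops will then start".

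The same recruitment stage mentions blood pressure and weight, taken "at an individual visit after the informative meeting", and a request for a lipid profile. It does not mention the questionnaires.

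On the outcome, Method/Design states "Principal Variable: HRQOL measured by means of SF-36 Questionnaire" and justifies the choice "as it is sensible to small changes". On the comparator: "The control group will continue to receive normal attention and will have the possibility, if they so desire, of doing the Health Workshops", once the 12-month evaluation is over and if the workshops prove effective. The Data analysis section takes the difference between the starting and final SF-36 ratings as the dependent variable of the regression models, and otherwise relies on paired before-after tests.

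**The concern.** A baseline should be measured when the two arms are still exchangeable, which means before allocation can influence the answers. Here the only stated limit is the start of the workshop, and that comes after allocation. For controls the limit is vaguer still, because they attend no workshop during follow-up.

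Allocation is evident to participants: either they attend a workshop, or they continue usual care with a conditional offer a year later. Persons interested fill in an application form for the workshop, so disappointment on one side and anticipation on the other are credible. The main outcome is the participant's own rating, chosen for its sensitivity to small changes. Because the models use the start-to-end difference, anything that moves the starting rating differently in the two arms enters the effect estimate. A larger sample does not remove it. Adjusting for baseline reduces it but does not remove it, because the covariate has itself been affected by allocation.

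**Working it through.** **1. Order of events in the text**

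| Event | Where stated | Position relative to allocation |
|---|---|---|
| Consent and recruitment | Recruitment stage | Before |
| Blood pressure, weight, lipid request | Recruitment stage | Described there, but not explicitly placed before allocation |
| Random assignment | Recruitment stage; stage forming the groups | - |
| Workshop starts | Stage forming the groups | After |
| Baseline SF-36, activity and diet forms | Gathering of information | Before the workshop; no limit set by allocation |

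The article is inconsistent on the unit of randomisation: primary care teams in the design paragraph, consenting persons in the description of the study. On both readings allocation follows recruitment and precedes the workshop, so the window between allocation and workshop exists either way.

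**2. Effect on the change score**

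Estimate = (end_I - base_I) - (end_C - base_C), where I is the workshop arm and C the control arm.

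Let knowledge of the arm shift base_I - base_C by d, and let a fraction k of that shift (between 0 and 1) still be present in the end ratings. Then

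bias = k·d - d = -(1 - k)·d.

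- k = 0 (the shift is confined to baseline): bias = -d, the largest size.
- k = 0.5: bias = -d/2.
- k = 1 (the shift persists fully): bias = 0.

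If controls rate themselves low through disappointment, or workshop participants rate themselves high in anticipation, then d > 0. The bias is negative and works against the workshop.

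With baseline adjustment instead of a plain change score, and k = 0, the bias is -β·d, where β is the slope of the end rating on baseline. For an assumed correlation of 0.5 and equal SDs, β = 0.5, so an assumed d of 3 leaves 0.5 × 3 = 1.5 points.

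**3. Scale, for illustration only**

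The point carries no figure of its own. For the number analysed I first reproduce the stated 108 per group. The article gives a 20% difference without a reference proportion; 40% versus 60% is an assumption. Arcsine formula: n = 2·[(1.960 + 0.842)/h]², with h = 2·asin(√0.6) - 2·asin(√0.4) = 0.403. This gives 96.8, so 97, and 97/0.9 = 107.8, so 108, which matches.

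Further assumptions: 97 analysed per arm, correlation 0.5 between baseline and end, no clustering, k = 0. The SF-36 SD is not given, so I take 10 and 20.

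SE = SD·√[2(1 - 0.5)]·√(2/97), which is 1.44 for SD 10 and 2.87 for SD 20. The true difference detectable with 80% power is (1.960 + 0.842)·SE: 4.02 points for SD 10 and 8.05 points for SD 20.

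Rejection with no true effect = Φ(d/SE - 1.96) + Φ(-d/SE - 1.96). Power for the detectable difference Δ when the bias is -d = Φ((Δ - d)/SE - 1.96).

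| Assumed d (points) | Rejection with no true effect, SD 20 / SD 10 | Power after bias (80% without it), SD 20 / SD 10 |
|---|---|---|
| 2 | 11% / 29% | 56% / 29% |
| 3 | 18% / 55% | 42% / 11% |
| 5 | 41% / 94% | 18% / 0.4% |

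Under the mechanisms above, the extra rejections in the middle column would favour the control arm. The right-hand column is the more relevant one: it shows a real benefit being missed. Clustering would enlarge the SE and change these percentages; it would not change the bias itself.

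**The case against.** The strongest reply is that the article never says the forms follow allocation. A questionnaire completed at consent would also satisfy the stated schedule, Figure 1 may show exactly that, and a condensed article may leave visit-level detail to the full protocol. This stands to the extent that a reader who infers that the plan schedules the baseline after allocation goes further than the text. It does not remove the point. The article does state a baseline rule, and the limit it names lies on the wrong side of allocation.

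Three further inferences are tempting and not supported.

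- **Later workshops leave people waiting after allocation.** At 12 to 15 people per workshop, 108 participants need about 8 to 9 workshops (108/15 = 7.2; 108/12 = 9). Nothing says they run one after another; varied schedules across several centres are compatible with parallel groups.
- **Blood pressure and weight are certainly taken before allocation, so the questionnaires are treated differently.** The visit is described in the recruitment stage, but no sentence puts it before assignment, and the list of variables says these measurements come from the computerised clinical history.
- **The bias equals the baseline shift.** That is true only if none of the shift persists to follow-up.

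It is also fair to say that an open, self-reported outcome is exposed to reporting bias at follow-up whatever is done at baseline. The fix closes one source of bias and leaves that one.

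**Conclusion.** The point holds as a weakness in the stated timing rule. The baseline SF-36, activity and diet questionnaires are anchored to the workshop, allocation precedes the workshop, and so the text allows a baseline completed with knowledge of the arm. Whether this will happen cannot be determined from the article.

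If it does happen, the change-score estimate is biased by up to the size of the differential baseline shift, and by less if the shift persists. That size is unknown: 2 to 5 points is an assumption, and the percentages above also rest on assumed SDs, correlation and number analysed, with clustering ignored. A reader might take the raised rejection rates as a risk of falsely claiming benefit. The mechanisms considered point the other way, mostly towards hiding one.

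The change is worth making because it is almost free and the analysis cannot fully repair the problem afterwards.

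**What to change.** In the paragraph on the gathering of information, re-anchor the first time point: in both arms, the baseline SF-36, activity and diet questionnaires are completed after consent and before the allocation of the team or person is generated or disclosed. The individual visit described in the recruitment stage would serve, provided that it precedes assignment; the text should say whether it does. If the forms are already completed before allocation in practice, the sentence only records that.

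Cost: a change of order. If that visit precedes assignment, no visit is added. The sample size is unaffected. The one downside is that the baseline may be somewhat older for any workshop that starts later.
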